### Palestinian context

Maternal and child health forms an important part of the healthcare system in Palestine. There are approximately 60,000 live births in the West Bank annually, and 99% are reported to be delivered in hospitals [22]. In 2014, the Palestinian Ministry of Health (MoH) operated 418 primary healthcare clinics (PHC) in the West Bank, and the majority of them provided antenatal care (ANC) services. PHC operated by the Palestinian MoH are classified from level 1 to 4 according to the healthcare services they provide. Level 1 PHC typically operate only once a week with a single healthcare provider, whereas level 4 PHC operate several days a week and with different health workers including specialists. ANC services are offered at all levels, but labor and delivery services are not provided in primary healthcare. Women have predefined PHC where they go for their ANC visits based on their residential address. According to the annual report published by the Palestinian MoH in 2016, adherence to at least one ANC visit is 98%, and to four visits 94%. About 45% of pregnant women in the West Bank receive ANC in PHC operated by the Palestinian MoH, with an average of 4.8 visits per woman. ANC is also provided by private clinics and the United Nations Relief and Works Agency for Palestine Refugees in the Near East (UNRWA). Comprehensive pregnancy risk management is provided at so-called high-risk clinics. There are 86 high-risk clinics in the West Bank and in 2015, 14% (*n* = 4415) of women receiving ANC in PHC operated by the Palestinian MoH were referred to a high-risk clinic for management. The Palestinian National Institute of Public Health (PNIPH) and the Palestinian MoH are currently rolling out a nationwide electronic registry (eRegistry) for maternal and child health. The implementation is undertaken in collaboration with and building on the eRegistries Initiative, tools, and implementation guidance, developed by the Norwegian Institute of Public Health in collaboration with the World Health Organization, the University of Oslo, and global RMNCH experts [10, 23]. The eRegistry for Palestine is developed in the District Health Information System 2 (DHIS2) tracker software, which is a flexible web-based open-source information system. All Palestinian residents have unique identifiers which makes it possible to track care and outcomes of women throughout pregnancy, childbirth, and the postpartum period, irrespective of the healthcare facility level. In this setting, currently operating only with paper case notes, we aim to assess the effectiveness of an eRegistry’s interactive checklists and clinical decision support on improving the quality of care for pregnant women.

### Objectives

#### Primary objectives

To estimate the effectiveness of the eRegistry’s interactive checklists and clinical decision support on: 1) improving the provision of timely and appropriate screening and management for important conditions during ANC; and 2) health outcomes for the mothers and the newborns.

#### Secondary objectives

To estimate the effectiveness of the eRegistry’s interactive checklists and clinical decision support on: 1) timely ANC visits; and 2) occurrence of stillbirths.

## Methods

### Trial design

This cluster randomized controlled trial (CRCT) is a superiority trial with two parallel arms (intervention and control). The unit of randomization is the individual PHC or, for the smallest units, clusters of two or three PHC. The randomization was undertaken by a statistician not otherwise involved in the trial.

### Study setting

The national public health system in Palestine currently uses paper-based files and reporting. An antenatal record is opened at the first ANC visit at the PHC. This record includes the personal ID number and name; socioeconomic information such as address, mother’s years of education, age at marriage and age at first pregnancy, monthly household income, and number of members in the household; obstetric information from the current and previous pregnancies such as parity, gestational age, last menstrual period, estimated date of delivery, and conception during breastfeeding; medical and surgical conditions; and family history of diseases (diabetes mellitus, hypertension, renal disease, etc.). Risk assessments are conducted at the first ANC visit, and women identified with certain risk factors are referred for further management in so-called high-risk clinics. Ultrasound scans during pregnancy are performed at the PHC. Monthly reports on aggregate data are sent from all PHC, high-risk clinics, and hospitals to the Palestinian MoH. Previous research of RMNCH services at different levels of the healthcare system in Palestine suggests considerable room for improvement [24]. Problems identified during stakeholder discussions as contributing to lower quality of care were sizable variations in the quality of care provided and ineffective ANC content despite frequent visits. Stakeholders in Palestine also identified several inefficiencies in the workflow in the PHC, due to redundant paperwork and reporting. Recommendations provided by Palestinian and international experts for the national health system include immediate action to support standardized practice guidelines, minimize inefficiencies, and promote better health information systems in RMNCH [24].

### Eligibility criteria

The inclusion criteria were PHC located in Bethlehem, Jenin, Nablus, Ramallah/Al-Bireh, and Salfit governorates offering ANC services reporting to the Palestinian MoH, including PHC following the national guidelines and workflows but jointly operated by the Palestinian MoH and nongovernmental organizations (NGO). We excluded PHC defined as level 1 or with no pregnant women enrolled in 2013 (due to small cluster sizes), PHC with a high-risk clinic at the same location (because all referral PHC providing high-risk management must receive the eRegistry’s interactive checklists and clinical decision support to enable the continuity of care and maintain information flow for women from the intervention clusters), and PHC participating in another health system study addressing the quality of ANC. A total of 133 PHC were eligible for randomization (Fig. 1). These PHC enrolled 8061 (mean 60.6 and median 53.0) new pregnant women in 2013. All new enrollments (women visiting the PHC for ANC services for the first time in the current pregnancy) in the eligible PHC will be counted towards outcome measures of the study. As a health systems research study, there are no eligibility criteria related to individual women’s characteristics.

**Fig. 1 Fig1:**
[figure not shown]
Flow diagram showing eligibility screening and recruitment of primary healthcare clinics (*PHC*). *We have grouped 25 small clinics in terms of annual number of newly enrolled preganancies (cluster size) to form 11 contiguous pairs and 1 contguous group of three clinics. The remaining PHC (*n* = 108) are individual clusters of their own, resulting in 120 clusters in total. *MCH *Maternal and Child Health, *MoH* Ministry of Health

### Intervention

Care providers in the intervention PHC have received the eRegistry’s interactive checklists with clinical decision support. During the first 3–6 months, all intervention PHC had both paper and electronic files, as only new enrollments of pregnancies are included in the eRegistry. Care providers in the control PHC will continue using the current system of paper-based files throughout the trial period. In terms of the national implementation, the control PHC will receive the eRegistry at a later stage than the intervention PHC.

#### Intervention tool

The intervention tool is the eRegistry’s interactive checklists and clinical decision support for ANC (Table 1). The interactive checklists and the current paper-based files include the same items and data points. The eRegistry allows for seamless incorporation of clinical workflow and guideline support in addition to reminders of daily clinical procedures and referrals (Table 1). All intervention PHC have been provided with desktop computers to be used by care providers in the consultation rooms. Care providers enter data on pregnant women into the eRegistry at the point-of-care (Table 1), and this data entry triggers the guideline-based decision support system (Figs. 2, 3 and 4). Each user has a unique username and password identifying their authorized access to the eRegistry in Palestine, with functionalities defined by their roles. The eRegistry is accessed by care providers using a Google Chrome browser. The full extent of the intervention is available at the demonstration eRegistry website which can be accessed through the link provided in reference [25].

**Fig. 2 Fig2:**
[figure not shown]
Intervention: illustration of interactive checklists. The top bar shows computed age, risk status, expected date of delivery (*EDD*), management status, gestational age at visit, and obstetric score

**Fig. 3 Fig3:**
[figure not shown]
Intervention: illustration of clinical decision support. Clinical decision support shows chronic hypertension on the right panel in response to high blood pressure values at a gestational age of 12 weeks

**Fig. 4 Fig4:**
[figure not shown]
Intervention: illustration of clinical management reminders. The bottom panel shows routine management reminders according to the antenatal care visit (folic acid supplementation, first routine ultrasound) and management support for the identified risk condition (referral to high-risk clinic and specialist)

#### Adherence

The eRegistry will fully replace the paper-based system. It is mandatory for use by care providers in the public health system in the intervention areas. Care providers in the intervention PHC have been trained on how to contact support staff in case of any problems with the software or infrastructure. Standard operating procedures (SOP) of the eRegistry in Palestine include routines for replacing malfunctioning computers and providing a back-up wireless internet solution within 24 h in case of internet disruption. The SOP also include measures for routine monitoring of use of the eRegistry and periodic data quality checks [26].

#### Concomitant care

The women seeking care in the intervention and control PHC will not receive any differential interference or concomitant care. The treatment guidelines were set by the Palestinian MoH, who were also responsible for the training and implementation of guidelines irrespective of allocation in this CRCT. The Palestinian MoH conducted a guidelines training session for intervention and control PHC in January 2016. The PNIPH, Palestinian MoH, and the Norwegian Institute of Public Health collaborate closely with the researchers of this CRCT, and have a common understanding of the importance of nonpreferential management of PHC. Any guideline change during the course of the CRCT will be applied to both the intervention and control PHC. The Palestinian MoH staff, referred to as maternal and child health supervisors that are typically nurses, carry out similar periodic supervision visits to all PHC in both arms of this CRCT.

### Outcomes

The focus of the outcome measures have been informed by national stakeholder consultations as representing key areas of quality concern in the Palestinian context, and to serve as sentinel outcomes for the overall quality of care. The adverse pregnancy outcomes reflect conditions that put the baby and/or mother at risk during labor or after delivery, and that could or should have been identified and/or managed prior to labor and delivery. The process (adherence) outcomes (Table 2) for the screening and management of the risk conditions and the corresponding adverse pregnancy outcomes (Table 3) will be assessed as primary outcomes. We have defined indicators to measure the process (adherence) outcomes (Additional file 1) based on the current guideline-based algorithms for management of conditions during ANC in Palestine (Additional file 2). Secondary outcomes are given in Table 4.

**Table 2 Tab2:** Primary process (adherence) outcomes, source of data, measurement sequence, and definitions

Process (adherence) outcomes	Source of data	Measurement sequence	Definitions
Timely and appropriate screening and management of anemia during pregnancy	Case records data from the PHC in the eRegistry	Registrations continuously at point of care, data export to the trial monthly	Proportion of women attending ANC who receive: 1. anemia screening at booking, and 2. screening at any ANC visits at 24 and 36 weeks if no anemia detected, and 3. rescreening after 1 month if mild or moderate anemia is detected, and 4. referred to high-risk clinic if refractory mild or moderate anemia is detected, and 5. referred to hospital if severe anemia is detected.
Timely and appropriate screening and management of hypertension in pregnancy	Case records data from the PHC in the eRegistry	Registrations continuously at point of care, data export to the trial monthly	Proportion of women attending ANC who receive: 1. blood pressure measurement at booking visit, and 2. blood pressure measurement at every ANC visit, and 3. appropriate laboratory tests for mild hypertension, and 4. referred to high-risk clinic hospital for chronic or gestational hypertension, and 5. referred to hospital for hypertension with proteinuria or signs of eclampsia.
Timely and appropriate screening and management of abnormal fetal growth	Case records data from the PHC in the eRegistry	Registrations continuously at point of care, data export to the trial monthly	Proportion of women attending ANC who receive: 1. first fundal height measurement at 16–20 weeks, and 2. fetal growth monitoring at every ANC visit, and 3. referred to ultrasound if discrepancy between fundal height and gestational age, and 4. referred to high-risk clinic if ultrasound confirmed fetal growth restriction.
Timely and appropriate screening and management of diabetes in pregnancy	Case records data from the PHC in the eRegistry	Registrations continuously at point of care, data export to the trial monthly	Proportion of women attending ANC who receive: 1. diabetes screening at booking, and 2. screening with random blood sugar test at 24–28 weeks, and 3. referred to high-risk clinic if random blood sugar test or glucose challenge test ≥ 140 mg/dl.

*ANC* antenatal care, *eRegistry* electronic registry, *PHC* primary healthcare clinics

**Table 3 Tab3:** Primary adverse pregnancy outcomes, source of data, measurement sequence, and definitions

Adverse pregnancy outcomes	Source of data	Measurement sequence	Definitions
Moderate or severe anemia at admission for labor	Hemoglobin admission data from hospitals in the eRegistry (public, private, and NGO hospitals)	Registrations continuously at point of care, data export to the trial monthly	Moderate anemia: hemoglobin greater than 7 and less than 9 g/dl; severe anemia: hemoglobin < 7 g/dl
Severe hypertension at admission for labor	Blood pressure admission data from hospitals (public, private, and NGO hospitals) in the eRegistry	Registrations continuously at point of care, data export to the trial monthly	Severe hypertension: systolic blood pressure ≥ 160 mmHg and/ or diastolic blood pressure ≥ 110 mmHg
Malpresentation at delivery undetected during pregnancy	Presentation at delivery data from hospitals (public, private, and NGO hospitals) in MCH registry	Registrations continuously at point of care, data export to the trial monthly	All non-cephalic presentations at or after 36 weeks of gestation and at labor
Small-for-gestational age baby at delivery undetected during pregnancy	Birth weight data from hospitals (public, private, and NGO hospitals) in the eRegistry	Registrations continuously at point of care, data export to the trial monthly	Small for gestational age: less than 2549 g [34]
Large for gestational age baby at delivery	Birth weight data from hospitals (public, private, and NGO hospitals) in the eRegistry	Registrations continuously at point of care, data export to the trial monthly	Large for gestational age: greater than 3980 g [34]

*eRegistry* electronic registry, *MCH *Maternal and Child Health, *NGO* nongovernmental organization

**Table 4 Tab4:** Secondary outcomes, source of data, measurement sequence, and definitions

Secondary outcomes	Source of data	Measurement sequence	Definitions
Timely ANC visits	Case records data from the PHC in the eRegistry	Registrations continuously at point of care, data export to the trial monthly	Proportion of women attending ANC who receive timely ANC visits according to guidelines at: 1. booking visit 2. 16 weeks gestation 3. 18–22 weeks gestation 4. 24–28 weeks gestation 5. 32 weeks gestation 6. 36 weeks gestation
Timely and appropriate screening and management of malpresentation ≥ 36 weeks	Case records data from the PHC in the eRegistry	Registrations continuously at point of care, data export to the trial monthly	Proportion of women attending ANC who receive: 1. screening for fetal presentation at any visit ≥ 36 weeks, and 2. referred to hospital for non-cephalic presentation
Stillbirth	Stillbirth data from the hospitals (public, private, and NGO hospitals) in the eRegistry	Registrations continuously at point of care, data export to the trial monthly	Baby born with no signs of life at or after 28 weeks of gestation

*ANC* antenatal care, *eRegistry* electronic registry, *NGO* nongovernmental organization, *PHC* primary healthcare clinics

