### Sample size

Sample size calculations for primary outcomes were performed in STATA (StataCorp. 2015, Stata Statistical Software: Release 14; College Station, TX, USA) “clustersampsi” using a 5% significance level and an assumed a priori intracluster correlation coefficient (ICC) of 0.01 for adverse pregnancy outcomes and 0.04 for the process outcomes [27]. Table 5 shows the estimated prevalence of primary outcomes for sample size calculations. We made sample size calculations to achieve a power of 90% based on an estimated average number of new pregnancies for 8 months in the study PHC. With 120 clusters recruiting for 8 months (with a minimum average cluster size of 44 in the year 2013), we will have more than 90% power to detect a relative 25–30% change in the composite adverse pregnancy outcome. With this sample size, we will have more than 90% power to detect a 15–25% change in the process primary outcomes. Effects of clustering and unequal cluster sizes have been accounted for in the sample size calculations (design effect = 1.75 for adverse pregnancy outcomes and 3.99 for process outcomes, and coefficient of variation of cluster size = 0.85) [28].

**Table 5 Tab5:** Assumed prevalence for primary outcomes for calculations of sample size

Outcome measure	Control group prevalence
Adverse pregnancy outcomes: composite of any of the five conditions below, accounting for coexistence of conditions in 10% of women	0.145
1. Moderate or severe anemia at admission for labor	0.0225
2. Large-for-gestational age baby at delivery	0.054
3. Small-for-gestational age baby at delivery undetected during pregnancy	0.057
4. Malpresentation at delivery undetected during pregnancy	0.02
5. Severe hypertension at admission for labor	0.01
Process (adherence) outcomes	0.40–0.60

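### The SGA and LGA components of the primary composite use one birth-weight cut-off at every gestational age, so they measure low and high birth weight rather than size for gestational age

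*Protocol article*

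**What the plan says.** Outcomes, Table 3, gives the two definitions as "Small for gestational age: less than 2549 g" and "Large for gestational age: greater than 3980 g", both with the same citation. The data source listed for each is "Birth weight data from hospitals (public, private, and NGO hospitals) in the eRegistry". No gestational age at delivery, centile, sex or term restriction is attached. Under Eligibility criteria the protocol sets no criteria at the level of the woman, so preterm births are included.

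Elsewhere the protocol does use gestational age. Malpresentation in Table 3 is defined as "All non-cephalic presentations at or after 36 weeks of gestation and at labor", and stillbirth in Table 4 as "Baby born with no signs of life at or after 28 weeks of gestation". Study setting lists "parity, gestational age, last menstrual period, estimated date of delivery" among the items in the antenatal record. The matching process outcome for abnormal fetal growth (Table 2) triggers an ultrasound referral when fundal height disagrees with gestational age.

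Table 5 (Sample size) assumes a control prevalence of 0.057 for "Small-for-gestational age baby at delivery undetected during pregnancy" and 0.054 for LGA, within a composite of 0.145.

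**The concern.** Size for gestational age is a comparison with babies of the same gestational week. A single weight threshold makes no such comparison, and it misclassifies in three ways:

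- A normally grown preterm baby under 2549 g is scored as SGA that antenatal care failed to detect, although fundal-height monitoring had no discrepancy to find.
- A growth-restricted baby born late and weighing more than 2549 g is not scored.
- A preterm baby that is large for its week but under 3980 g is not scored.

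The Outcomes section says the adverse outcomes are conditions that could or should have been identified or managed before labour, and that they correspond to the process outcomes. For fetal growth, the process outcome is indexed to gestational age and the health outcome is not.

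Two things are at stake. A result reported as SGA or LGA would not mean that. Events that reflect when a baby was born rather than how it grew may also dilute an effect on the composite.

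**Working it through.** **1. Inputs.** From Sample size and Table 5: 120 clusters of mean size 44; coefficient of variation (CV) of cluster size 0.85; intracluster correlation (ICC) 0.01 for adverse outcomes; 5% significance level; composite control prevalence 0.145; components 0.0225, 0.054, 0.057, 0.02 and 0.01. From Allocation: 1:1. From Statistical methods: two-sided tests.

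**2. The plan's own design effect.** 1 + ((1 + CV²) × m − 1) × ICC = 1 + ((1 + 0.7225) × 44 − 1) × 0.01 = 1.748. The stated 1.75 is reproduced.

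**3. Effective sample size.** 60 × 44 = 2640 women per arm, and 2640 / 1.748 = 1510.

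**4. Baseline power.** For two proportions with n = 1510 per arm (pooled variance under the null), control 0.145 against 0.145 × (1 − 0.269) = 0.106 gives 90%. A 26.9% reduction is therefore about the smallest that reaches 90% power. It lies inside the stated 25–30% range. At exactly 25%, power is 85%.

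**5. Weight of the two components.** The components sum to 0.0225 + 0.054 + 0.057 + 0.02 + 0.01 = 0.1635. SGA plus LGA is 0.057 + 0.054 = 0.111, and 0.111 / 0.1635 = 68%. The next largest component is anemia, at 0.0225.

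**6. Possible dilution.** The documents give no preterm rate and no weight distribution by week, so the size is not computable. Let f be the share of births that are normally grown preterm babies, counted as SGA and unaffected by the intervention. This is an assumption. Table 5 does not say whether such babies are already in the 0.145, so two models are shown.

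- *Model A, already inside 0.145.* The true 26.9% reduction acts only on the remainder: observed reduction = 0.269 × (0.145 − f) / 0.145.
- *Model B, added to 0.145.* The absolute effect stays at 0.145 × 0.269 = 0.039 and the control prevalence becomes 0.145 + f.

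| f | f / 0.057 | Model A: observed reduction | Model A: power | Model B: control prevalence | Model B: power |
|---|---|---|---|---|---|
| 0 | 0% | 26.9% | 90% | 0.145 | 90% |
| 0.5% | 9% | 26.0% | 88% | 0.150 | 89% |
| 1% | 18% | 25.0% | 85% | 0.155 | 88% |
| 2% | 35% | 23.2% | 79% | 0.165 | 86% |

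The second column sets f against the assumed SGA prevalence of 0.057. Under Model A it is the share of that component made up of normally grown preterm babies.

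The table covers only one of the three misclassifications. The documents give nothing with which to size the other two.

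**The case against.** **The power loss rests on an outside assumption.** This is right. No value of f appears in the documents. A reader might carry the calculation to f = 4% and infer that power falls to 63%. That would make 0.04 / 0.057 = 70% of the assumed SGA prevalence normally grown preterm babies, and it also requires Model A. Under Model B the same f gives 82%. The documents support neither the value nor the choice of model.

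**The composite still means something.** A reader might infer that the result becomes uninterpretable. The Outcomes section presents these measures as sentinels of overall quality of care and of risk during labour or after delivery, not only as readouts of fetal growth. High absolute birth weight fits that purpose, and LGA has no condition about being undetected. The intervention also covers hypertension, diabetes and anemia, so it is not shown that the added events are beyond its reach. The same cut-offs apply in both arms. What stands is mislabelling and probable dilution; no false positive follows.

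**The cited reference may give week-specific values.** It is not available here. Even if these are the centiles for one week, Table 3 names no week and applies one value to every birth. Nor is this a detail that a condensed article leaves out: the definition is stated.

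**Gestational age may be dated differently by arm.** This is the strongest point, and it bears on the remedy. Hospital staff record birth weight effectively blinded to allocation (Blinding). Gestational age would come from the clinics. There the intervention tool computes gestational age and expected delivery date (Fig. 2), while control clinics work on paper. The fix has to allow for this.

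**Conclusion.** The point holds as a fault of definition. On the stated rule, components carrying 68% of the summed component prevalence are low and high birth weight under another name, although the protocol already describes the data needed to relate weight to gestational age. This conclusion needs no outside figure.

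The effect on power is illustrative only. For f between 0.5% and 2%, power for a 26.9% reduction falls from 90% to 88–79% under Model A, or to 89–86% under Model B. Both ranges assume that the intervention leaves those births unchanged. The documents support neither a specific power loss nor a claim that the composite is without meaning.

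**What to change.** In Table 3, define SGA as birth weight below the 10th centile and LGA as above the 90th centile for completed week of gestation at delivery, from one named reference. Compute gestational age by a single written dating rule, from the recorded last menstrual period or estimated date of delivery and the delivery date. Apply the rule identically in both arms, and do not use the tool's own computed value in one arm only. Recheck the SGA, LGA and composite prevalences in Table 5 on the new definition. Keep the 2549 g and 3980 g cut-offs as a sensitivity analysis, labelled low and high birth weight.

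The cost is revised derivation wording, a dating rule, a centile look-up table, a rule for births with missing gestational age, and the recheck of Table 5. The downside is that those missing values and possibly arm-dependent dating error enter a primary outcome. The fixed-cut-off analysis helps to check for this, because the weight cut-offs themselves do not depend on clinic dating.
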